### Procedure for unblinding if needed {17b}

No routine unblinding is planned, as the single-blind design only keeps participants unaware of their group assignment. Since the study staff are not blinded, they are aware of the intervention assignment and can access this information when medically necessary. The protocol emphasizes participant safety, which implies unblinding is allowed if it serves clinical care.

## Data collection and management

### Plans for assessment and collection of outcomes {18a}

Baseline data include medical and medication history, physical examination, and laboratory parameters such as hematology, biochemistry, HIV viral load, CD4/CD8 counts, and serology. Study outcomes will be assessed through clinical evaluation, laboratory assays, and validated research procedures at multiple time points across six study visits.

#### Outcome measures and instruments

Primary outcome: Changes in REG3α plasma levels (a validated marker of gut permeability) using ELISA.Secondary outcomes: Changes in inflammatory and gut permeability markers (e.g., I-FABP, LPS, β-D-glucan, cytokines) via ELISA or Multiplex assays, and immune activation markers via flow cytometry (HLA-DR, CD38, CD83, CD86).Exploratory outcomes: Microbiota composition via 16S rDNA sequencing and HIV reservoir size by qPCR.Sub-study measures: Gut architecture and immune activation assessed through paraffin-embedded biopsy immunostaining (e.g., claudin-3/occludin) and flow cytometry.

All instruments and assays have been validated and previously published by the team or others in peer-reviewed literature. Laboratory methods adhere to standard operating procedures (SOPs) including those from the International Human Microbiota Standards (IHMS).

#### Data quality assurance

All study personnel will be trained in good clinical practice (GCP) and study-specific procedures.Sample collection, processing, and storage follow strict protocols to preserve sample integrity.eCRFs will be used for data entry, with built-in validation rules and range checks.Duplicate testing will be performed for critical assays when feasible (e.g., ELISA replicates).Flow cytometry and sequencing assays will be performed by qualified laboratory personnel using validated gating and bioinformatics pipelines.

#### Source documentation and access

Source documents include medical charts, lab results, and signed consent forms. eCRFs will be considered the official data repository. The database will be managed under MUHC’s data security policies, with restricted access and audit trails.

#### Reference to data collection forms

All data collection forms (e.g., questionnaires, lab requisitions, eCRF templates) are maintained separately in the study’s operations manual and are available upon request but are not included in the protocol document.

### Plans to promote participant retention and complete follow-up {18b}

Participant retention and study completion are essential to the validity of the trial outcomes. The following strategies will be implemented to promote participant adherence and minimize loss to follow-up.

#### Retention strategies

Clear communication: Participants will receive detailed written and verbal instructions regarding study procedures, visit schedules, and the importance of completing all follow-up visits.Dedicated study staff: Participants will be followed closely by a consistent team of research coordinators, nurses, and investigators to foster trust and engagement.Appointment reminders: Reminders via phone, email, or text message will be provided prior to each study visit.Flexible scheduling: Study visits will be scheduled at convenient times for participants whenever possible, including early mornings or late afternoons.Participant engagement: A positive study experience will be encouraged through consistent communication, respectful interactions, and regular updates on study progress and findings.Incentives: Modest, ethically appropriate compensation will be provided for time and inconvenience, in accordance with REB-approved policies.

#### Follow-up and data collection for early withdrawals

If a participant discontinues or deviates from the assigned intervention, every effort will be made to retain them for follow-up assessments. This includes:Scheduling remaining study visits even if the participant is no longer receiving the study intervention.Documenting reasons for withdrawal or protocol deviations in the eCRF.oCollecting available clinical and laboratory outcome data at the time of withdrawal, including adverse events, vital signs, HIV viral load and CD4/CD8 counts, blood and stool samples for biomarker analysis (when feasible), and questionnaire data (e.g., AUDIT-C, symptom checklists)

#### Data inclusion

Participants who deviate from the protocol or discontinue early will still be included in the intention-to-treat analysis when appropriate. Efforts will be made to obtain final visit data to ensure robust outcome assessment and minimize missing data.

### Data management {19}

#### Data entry and coding

Data for this study will be recorded using eCRFs on the InForm platform, hosted on a secure, Health Canada-compliant clinical data management system. All study data will be entered into the system by trained research staff. Each participant will be assigned a unique study identifier to ensure confidentiality and facilitate accurate tracking.Source documents will include clinical charts, lab reports, and signed informed consent forms.Data will be entered from source documents into the eCRF as soon as possible following each study visit.All laboratory results will be coded using standardized variable names aligned with CDISC/MedDRA conventions where applicable.

#### Data quality control

To ensure high data quality and integrity, the following quality assurance procedures will be implemented:Automated range checks: The eCRF system will include validation rules and range checks to flag missing, inconsistent, or out-of-range values at the time of data entry.Query management: Data queries generated by the system or monitors will be addressed and resolved by site staff in a timely manner.Monitoring: Regular internal monitoring will be conducted to verify data against source documents. External monitoring will be performed in accordance with the study’s monitoring plan.

#### Data security and storage

All electronic data will be stored on password-protected servers compliant with institutional and regulatory data privacy standards. Access to the eCRF system will be role-based and restricted to authorized personnel. Data will be backed up regularly, and audit trails will be maintained to track all changes.Paper documents (e.g., consent forms, backup logs) will be stored in locked filing cabinets in a secure research office at the MUHC.Biological sample data will be linked to study IDs only, with no directly identifiable information attached.

#### Data retention and archiving

Data will be retained for a minimum of 25 years post-study completion, in accordance with Health Canada and institutional guidelines. At the end of the retention period, data will be securely archived or destroyed as per SOPs.

#### Reference to additional procedures

A detailed Data Management Plan (DMP), including system specifications, user access logs, SOPs, and data cleaning workflows, is maintained separately and is available upon request from the study investigator.

### Confidentiality {27}

Personal information of all potential and enrolled participants will be collected, managed, and stored with strict adherence to privacy regulations and institutional policies to ensure confidentiality is protected at all stages of the study—before, during, and after participation.

#### Collection and storage of personal information

Identifiable information (e.g., name, date of birth, health card number) will be collected solely for the purpose of screening, enrollment, and follow-up.Upon enrollment, each participant will be assigned a unique study ID. This ID will be used on all case report forms (CRFs), laboratory samples, and stored data.Personal identifiers will be stored separately from study data in a secure, access-restricted location at the McGill University Health Centre (MUHC).

#### Access and sharing

Only authorized members of the study team, including the principal investigator, research coordinators, and relevant regulatory monitors, will have access to identifiable participant information.Data shared with collaborators, laboratories, or external monitors will be de-identified and labeled with study IDs only.Any transfer of data outside the study site will follow data sharing agreements and comply with applicable privacy laws (e.g., Canadian Personal Health Information Protection Acts, GCP guidelines).

#### During and after the study

Identifiable information will not appear in any reports, presentations, or publications.All electronic data will be stored on encrypted, password-protected servers, with role-based access controls and full audit trails.Paper files will be stored in locked cabinets in secure areas with limited access.Confidentiality obligations apply indefinitely, even after the trial has ended.

#### Participant notification

Participants will be informed of these confidentiality protections in the informed consent process. They will also be told how their data will be used, how it will be protected, and that withdrawal from the study does not affect their rights to medical care or confidentiality.

### Plans for collection, laboratory evaluation, and storage of biological specimens for genetic or molecular analysis in this trial/future use {33}

Biological specimens including blood, stool, and optional colon mucosal biopsies will be collected at designated study visits for both clinical and research purposes, including molecular and immunologic analyses.Blood samples: Collected at visits 2, 3, 4, 5, and 6 (~60 mL per visit) for isolation of plasma, serum, and peripheral blood mononuclear cells (PBMCs).Plasma/serum will be analyzed for inflammatory markers, gut permeability biomarkers (e.g., REG3α, I-FABP, LPS, BDG), and cytokine profiles using ELISA and Multiplex.PBMCs will be analyzed by flow cytometry (e.g., CD4/CD8 T cell activation, PD-1 expression) and used for HIV reservoir quantification by nested qPCR and Tat/Rev Induced Limiting Dilution Assay (TILDA).Stool samples: Collected at visits 2 through 6 for microbiota analysis.DNA will be extracted and analyzed using 16S and 18S rDNA sequencing and metagenomic techniques to assess microbial composition, diversity, and donor engraftment.Colon mucosal biopsies (optional sub-study): Collected at visits 3 and 6 (for consenting participants).Biopsies will be fixed or frozen for immunohistochemistry (e.g., claudin-3/occludin, myeloperoxidase staining), immune cell isolation, and HIV reservoir quantification via qPCR or RNAscope.

All laboratory analyses will be performed by qualified personnel at the MUHC Research Institute and collaborating labs, using validated and standardized protocols.

#### Future use and storage

With participant consent, leftover biological specimens will be stored for potential future research on emerging biomarkers of gut permeability or immune activation, new methods for HIV reservoir quantification, advanced microbiome, or transcriptomic profiling.

Stored specimens will be de-identified and linked only to a study ID, frozen at −80 °C or in liquid nitrogen, depending on sample type and securely stored at the MUHC research laboratories under the supervision of the principal investigator.

Any future research using these specimens will require approval by an appropriate Research Ethics Board (REB) and must comply with applicable privacy laws and institutional policies.

Participants may opt in or out of specimen storage for future use during the informed consent process.

## Statistical methods

### Statistical methods for primary and secondary outcomes {20a}

#### Primary outcome analysis

The primary outcome, change in plasma REG3α levels (a marker of gut permeability), will be analyzed using a within-subject comparison (pre- (baselines 1 and 2) vs. post-intervention (weeks 6 and 12)) and between-group comparison (FMT vs. placebo).

Descriptive statistics will be used to summarize REG3α levels at each time point. Paired *t*-tests or Wilcoxon signed-rank tests will assess within-group changes over time, based on data distribution. Between-group differences in change from baseline will be assessed using independent *t*-tests or Mann-Whitney *U* tests. A 95% confidence interval for the mean difference will be reported.

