### Outcomes {12}

Table 1 is a structured summary of the primary, secondary, and exploratory outcomes, including the measurement variables, analysis metrics, methods of aggregation, time points, and clinical relevance.

**Table 1 Tab1:** Study outcome details

a. Primary outcome					
Outcome	Details				
Measurement variable	Plasma levels of REG3α (a marker of gut permeability)				
Analysis metric	Change from baseline compared between FMT and placebo groups				
Method of aggregation	Mean or median (analyzed using *t*-test or Wilcoxon rank sum test)				
Time points	Baseline (visits 2 and 3), week 6, and week 12				
Clinical relevance	REG3α is a key biomarker for gut epithelial damage and microbial translocation. Reducing REG3α suggests improved gut barrier integrity, which may decrease chronic immune activation in ART-treated PWH				
b. Secondary outcomes					
Outcome	Measurement variable(s)	Analysis metric	Method of aggregation	Time points	Clinical relevance
Safety and tolerability of FMT	Adverse events, hematology, serum chemistries (e.g., ALT, AST, glucose, lipids, hs-CRP, D-dimer)	Incidence/frequency; change from baseline, compared between FMT and placebo arms	Proportion; mean/median	Throughout study (all visits)	Evaluates whether FMT is safe and well tolerated in PWH
Markers of gut permeability	Plasma I-FABP, LPS, β-D-glucan	Change from baseline, compared between FMT and placebo arms	Mean/median (Multiplex, ELISA, Fungitell assay)	Baseline, week 6, week 12	I-FABP, LPS, and β-D-glucan are established indicators of gut epithelial damage and bacterial and fungal translocation
Inflammatory/anti-inflammatory cytokines	IL-1β, IL-6, IL-8, IL-17A/F, IL-22, IL-10, IL-37, IP-10	Change from baseline, compared between FMT and placebo arms	Mean/median (Multiplex or ELISA)		Evaluates whether FMT could reduce immune activation and decrease the risk of non-AIDS comorbidities
Immune cell activation	Flow cytometry of HLA-DR, CD38 on T-cells, CD83, CD86 on myeloid cells	Change from baseline, compared between FMT and placebo arms	Mean/median		
c. Exploratory outcomes					
Outcome	Measurement variable(s)	Analysis metric	Method of aggregation	Time points	Clinical relevance
Microbiota composition and diversity	16S, 18S rDNA sequencing, metagenomics in stool samples	Change from baseline, compared between FMT and placebo arms	Alpha/beta diversity metrics; LEfSe; DESeq2	Baseline, week 6, week 12	Identifies changes in microbiota profile

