#### Adjusted analyses

If relevant baseline imbalances are observed between the intervention groups, adjusted analyses may be conducted using multivariable linear or logistic regression models to control for potential confounders (e.g., age, baseline inflammatory marker levels, ART regimen duration).

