#### Statistical considerations

All additional analyses will be clearly labeled as exploratory. Results will be interpreted in the context of the small sample size and multiple comparisons and no formal correction for multiplicity will be applied in these exploratory analyses.

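### The primary REG3α comparison is an unadjusted change-score test with the t-or-rank choice left open; one pre-specified baseline-adjusted model would fix the estimand and usually gain some precision

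*Protocol article*

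**What the plan says.** In the protocol article, the section Primary outcome analysis sets the between-arm comparison: "Between-group differences in change from baseline will be assessed using independent" t-tests or Mann-Whitney U tests, with a 95% confidence interval for the mean difference. Table 1 under Outcomes {12} agrees. Its metric is "Change from baseline compared between FMT and placebo groups", it allows a mean or a median, a t-test or a rank sum test, and it names no covariate.

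The one stated basis for choosing a test belongs to the paired comparisons within each arm: "Wilcoxon signed-rank tests will assess within-group changes over time, based on data distribution". The between-arm sentence has no such clause.

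Adjustment comes up under Adjusted analyses: "If relevant baseline imbalances are observed between the intervention groups, adjusted analyses may be conducted". Statistical considerations then sets its status: "All additional analyses will be clearly labeled as exploratory".

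The REG3α time points in Table 1 are "Baseline (visits 2 and 3), week 6, and week 12", so each participant has two pre-treatment and two post-treatment values. Repeated-measures ANOVA or mixed models are named for the secondary outcomes. For the primary outcome they could apply only through the general provision for repeated measures under Handling missing data.

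**The concern.** There are two separate problems.

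- **The analysis is not fixed.** A t-test on mean change and a Mann-Whitney test answer different questions. An interval for a mean difference belongs to the first only; the usual partner of the rank test is an interval for a location shift. The choice would be made with the data in hand, and Table 2 lists data analysts as not blinded.
- **Precision may be given away.** A change score subtracts the whole baseline whatever its correlation with the outcome. ANCOVA estimates how much to subtract. At 10 per arm that can matter for partial effects, and the baseline values are already being collected.

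The trial is an exploratory pilot whose variance estimates are meant to support later power calculations, so how change is defined and analysed also affects what it hands on.

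**Working it through.** **The plan's own figure.** Sample size {14} gives 5 per group for 80% power, from 2441 ± 630 versus 715 ± 243 pg/mL. The difference is 1726 pg/mL, or 1726/630 = 2.74 SD using the larger SD. Noncentral-t power is 0.71 with 3 per group, 0.89 with 4 and 0.965 with 5. The stated 5 is therefore slightly conservative, and 10 per arm gives power near 1 with either analysis. Precision matters only for effects well short of full normalization.

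**Inputs for the comparison.** 10 per arm and two-sided 5% come from the article. Compound symmetry and the correlation ρ between any two REG3α values in a participant are assumptions; the article gives no ρ, so 0.3 to 0.9 is shown.

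**Formulas**, in units of the single-measurement variance, with p baselines and r post-treatment visits averaged:

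- Change score: (1+(r−1)ρ)/r + (1+(p−1)ρ)/p − 2ρ
- ANCOVA: [(1+(r−1)ρ)/r − pρ²/(1+(p−1)ρ)] × [1 + 1/(2n−4)]. With n = 10 the last factor is 1 + 1/16 = 1.0625, the small-sample cost of estimating the slope.

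Example with p = 2, r = 2, ρ = 0.5:

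- Change score: 0.75 + 0.75 − 1.00 = 0.50
- ANCOVA: (0.75 − 0.50/1.50) × 1.0625 = 0.4167 × 1.0625 = 0.443
- Ratio: 0.443/0.50 = 0.89

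**Ratio of ANCOVA variance to change-score variance, same measurements in both:**

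| Measurements | ρ=0.3 | ρ=0.5 | ρ=0.7 | ρ=0.9 | Break-even ρ |
|---|---|---|---|---|---|
| 1 baseline, 1 visit | 0.69 | 0.80 | 0.90 | 1.01 | 0.88 |
| 2 baselines, 1 visit | 0.87 | 0.94 | 1.00 | 1.04 | 0.70 |
| 2 baselines, 2 visits | 0.78 | 0.89 | 0.97 | 1.04 | 0.79 |

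**Power for a 1-SD effect, both baselines and both visits** (18 df for the change score, 17 for ANCOVA):

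| | ρ=0.3 | ρ=0.5 | ρ=0.7 |
|---|---|---|---|
| Change score | 71% | 85% | 97% |
| ANCOVA | 82% | 89% | 97% |

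**Test choice.** In a simulation at 10 per arm (15,000 runs, normal and lognormal data), choosing the test by a Shapiro-Wilk check gave a type I error of 0.048 to 0.049. Taking the smaller of the two p-values gave 0.053 to 0.057. The cost of the open choice is thus an unfixed estimand and a mismatched interval, with little false-positive inflation.

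**The case against.** An unadjusted change-score comparison is unbiased in a randomized trial. This is an exploratory pilot, and the article defers further statistical detail to an analysis plan to be finalized before database lock, which is not shown. The section Primary outcome analysis also names both baselines as the pre-treatment period, so averaging them is the more natural reading; at moderate to high correlation, most of the possible gain is then already in hand. All of this stands and limits the size of the point. It does not remove it, because the article itself positively sets the unadjusted test as primary and leaves adjustment exploratory.

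A reader might also infer four stronger things that the document does not support:

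- **A very large power gain.** At ρ = 0.5, a change score from one baseline and one visit has 56% power for a 1-SD effect, against 89% for ANCOVA on all four measurements. Most of that gap comes from averaging: the change score on all four already has 85%.
- **That observed imbalance decides the primary test.** The trigger governs only optional exploratory analyses. The primary test stays unadjusted whatever the baseline shows.
- **That anyone with a missing visit is dropped.** Handling missing data provides for multiple imputation and mixed models. Complete-case analysis is reserved for minimal missingness assumed to be completely at random.
- **That REG3α has been shown to be multiplicative.** The coefficients of variation, 630/2441 = 26% and 243/715 = 34%, are closer than the raw SDs, which suggests a log scale. But they come from two different populations, and all trial participants belong to the first.

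**Conclusion.** The point holds as a moderate improvement; the plan is not invalid. As stated, the primary analysis leaves the between-arm test unchosen, pairs a mean-difference interval with a possible rank test, and does not use baseline REG3α as a covariate. With both baselines and both visits in either method, adjustment cuts the variance by about 22%, 11% and 3% at correlations 0.3, 0.5 and 0.7. Over correlations 0.3 to 0.9 and the three measurement sets, the worst loss is about 4%, at 0.9.

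These sizes rest on compound symmetry and an assumed correlation. They also treat the two baselines as exchangeable. Intervention description {11a} places a bowel cleanse the day before the second baseline, so the two may not be exact replicates.

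**What to change.** Name one primary model: ANCOVA, or a mixed model with a small-sample degrees-of-freedom correction, for REG3α at weeks 6 and 12. Include arm, visit, arm-by-visit and baseline REG3α from visits 2 and 3.

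- State how the two baselines enter. Their mean is the simplest choice, with a check on whether values differ before and after the cleanse.
- Preferably analyse logs, and report the arm effect averaged over both visits as a geometric mean ratio with the 95% confidence interval from the same model.
- Keep one pre-set rank or re-randomization test as a sensitivity analysis, in place of the open choice between tests.
- State that baseline adjustment of the primary outcome applies regardless of observed imbalance.

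The cost is wording, model code and one degree of freedom if the mean baseline is used, with a slight loss of precision if the correlation proves very high. No new data are needed. The Trial status section reports data collection as still in progress, so at that stage the change could be written into the analysis plan before database lock.

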#### Secondary outcome analysis

Secondary outcomes include changes in inflammatory and gut permeability markers (e.g., I-FABP, LPS, cytokines), immune activation markers (e.g., HLA-DR, CD38 on T cells and CD83, CD86 on myeloid cells), and safety and tolerability outcomes (e.g., adverse events, hematology, HIV viral load).

These will be analyzed using repeated measures ANOVA or mixed-effects models to evaluate group-by-time interactions, non-parametric tests where assumptions are violated, and categorical variables (e.g., adverse event incidence) analyzed using chi-square or Fisher’s exact test.

All tests will be two-sided with a significance level set at *α* = 0.05.

